### Participants

#### Inclusion

Individuals will be eligible if they meet all of the following criteria:Have smoked ≥10 cigarettes per day for the last 6 monthsSmoke first cigarette within 90 min after wakingAge 18 to 60 yearsVision normal or corrected to normal (to ensure that they can accurately see the images on the screen and select the appropriate response)Willing to complete all appointments and change smoking behaviors for 2 weeksHave made no quit attempts or attempts to cut back in the last 30 daysHave no plans to quit in the next 30 daysHigh school graduate or GED.

#### Exclusion

Individuals will be ineligible if they report any of the following:Serious medical illness unsuitable for the MRI scanner based on best clinical judgmentAny history or current symptoms of neurologic or psychiatric disorders except depression, anxiety, or attention-deficit disorder/attention-deficit hyperactivity disorderCurrently taking anti-seizure medicationHistory of concussionBody mass index >50Left-handed, due to differences in neural organization between right-handed and left-handed individualsHistory of alcohol or other substance dependence or current abuseRisk for hazard due to magnetic fields, such as metal in the body due to surgery or an accident (e.g., a pacemaker, cochlear implants, aneurysm clips, intravascular stents or coils, spinal shunt, injury involving bullets, shrapnel or metal implanted in their body, etc.)Pregnancy.

Final eligibility will be adjudicated by the principal investigator.

#### Recruitment

Smokers will be recruited from the Kansas City metropolitan area (population of 2.3 million) using recruitment methods used successfully in the past, including the internet (e.g., Craigslist and Facebook), print, and media advertising (e.g., radio and television spots). Prospective participants will be given a phone number, email address, and website URL to contact for screening. We will also recruit participants from our Clinical Translational Science Award-sponsored Frontiers registry (NIH UL1TR000001), which is a list of smokers who have agreed to be contacted for research studies. All study procedures will take place at the University of Kansas Medical Center, Kansas City, MO, USA.

### Study procedures

#### Consent appointment (day 0)

Study staff will review consent forms describing study goals, procedures, risks, and confidentiality with each participant. Those who consent to participate will be enrolled in the study and given instructions on how to prepare for the baseline session, which will include the first fMRI assessment and daily monitoring of smoking behaviors (days 1–7). In addition, demographic information (including age, gender, education, and income), smoking history, and other data will be collected at the consent appointment. Figure 2 is a full list of questionnaires and tasks administered and the timing of their administration. To promote retention, participants will be compensated for completing questionnaires (Additional file 1).

**Fig. 2 Fig2:**
[figure not shown]
Study measures and timing (SPIRIT Figure). Cigs cigarettes, *MRI* magnetic resonance imaging, *QSU* Questionnaire of Smoking Urges, *UPPS-P* Urgency, Premeditation, Perserverance, Sesation-Seeking, and Positive Urgencey

#### Daily monitoring (days 1–7)

Smoking behaviors will be measured using portable Micro+™ basic Smokerlyzer® CO monitors (coVita, Santa Barbara, CA, USA). The CO monitors come with software that records their output, such as CO levels and a timestamp of each CO measurement. A baseline level will be collected at the beginning of the consent appointment for comparison with levels at the scanning appointments. At this appointment, we will also show participants how to use the CO monitor and instruct them to use it daily during the study. For 1 week following the initial consent appointment, participants will be asked to smoke as usual and provide CO levels by blowing into the CO monitor mouthpiece: (1) upon waking, (2) immediately before smoking the first cigarette of the day, (3) 5 to 10 min following smoking the first cigarette of the day, and (4) immediately before smoking the second cigarette of the day. This will provide timestamps for when participants typically smoke their first and second cigarettes of the day, which will be used as a guide for how long participants in the practice group will be asked to delay smoking their first cigarette.

Participants will also complete paper-and-pencil daily logs recording their first two cigarettes and answering questions relating to their smoking behavior, such as how many cigarettes they smoked that day and if a day was considered typical. Participants will be contacted on days 1 and 3 to see if they are having any difficulty using the monitor and to address any questions. Participants who consent to receiving texts will receive text prompts on days 2 and 4 to remind them to use their CO monitor.

#### Pre-treatment scan appointment (day 7)

Participants will be asked to smoke as usual on the days of testing. They will be given an opportunity to smoke immediately prior to their appointment but not again until they complete testing (about 3–4 h later). This will be done to minimize the dampening effect on cue reactivity of smoking expectancy [18, 25], to control for the time of the last cigarette, and to minimize participant burden. Their height and weight will be measured. There will be at least a 2-h abstinence period prior to the MRI scans. During this time, participants will fill out self-report questionnaires, complete neuropsychological tests, and will be asked to provide a CO measurement. Other studies have used similar abstinence periods and seen expected brain activation patterns to smoking cues [26–31].

Following the fMRI scan, all participants will receive a 10-min CBT style counseling session in which a trained counselor will discuss how to cope with smoking urges, emphasizing problem-solving to overcome difficulties encountered when practicing delaying the first cigarette of the day. We will provide these tips to all participants prior to randomization to control for the influence of the brief counseling on brain activation changes. Without this control, it would be difficult to identify whether brain changes observed in the practice group are due to the brief counseling session or the daily practice of delaying the first cigarette. To promote retention and completion of daily questionnaires, participants will be compensated at the second visit for their time, for completing the one week of CO measurements

#### Randomization and blinding

Following the brief counseling, participants will be randomized using a 1:1 allocation ratio to the practice or no practice arm of the study. Groups will be stratified on gender and marijuana use to prevent these variables from confounding treatment effects. Based on previous recruitment data, we expect a 1:1 ratio of men to women and a 1:2 ratio of marijuana users to non-marijuana users. Separate blocked randomization sequences (www.randomization.com) for each of the four strata will be used. A person from outside the study team, who will have no interaction with the participants or the data, will generate the sequence and reveal the group assignments prior to building the practice schedule. Staff responsible for enrolling subjects will not participate in generating the randomization sequence and will not have specific knowledge of how it was generated.

Study staff who interact with participants will be blinded to group membership until after the brief counseling session. They will not be informed of group membership until it is time to reveal it to the participants. Participants will not be blinded to group membership because there is no way to institute the intervention without revealing group membership.

#### Intervention (days 8–21)

For 2 weeks following the initial fMRI appointment, CO levels will be recorded daily by having the participant blow into the CO monitor mouthpiece upon waking, immediately before smoking the first cigarette of the day, 5 to 10 min following smoking the first cigarette of the day, and immediately before smoking the second cigarette of the day. This will provide data on adherence to delaying or not delaying the first cigarette of the day as instructed. Participants will receive a follow-up phone call or text on day 8 to see how the use of the monitor is working and/or how practicing delaying the first cigarette of the day is going. In addition, we will address any participant questions. Participants who consent to receiving texts will also receive text prompts on days 9, 11, 16, and 18 to remind them to use their CO monitor and/or ask how practicing delaying the first cigarette of the day is going.

##### Practice group

Half of the participants will be randomized to the practice group. Data from self-reported typical days from the initial week of monitoring will be averaged to build participants’ schedules (Table 1). To standardize practice for our experiments, we will ask smokers to delay their first cigarette of the day on a progressive schedule for 1 week with the goal of delaying their first cigarette to the time of their usual second cigarette of the day or later. The maximum delay will be maintained during the second week for a total of 2 weeks of practice. On day 14, practice group participants will be sent a text asking, “On a scale from 1 to 5: 1 = not at all difficult and 5 = extremely difficult – how difficult would you say delaying your first cigarette has been the past two days?” If participants report a 1 or 5 for either day, they will be sent an adjusted schedule. In the case of a 1, the following 2 days will continue the progressive schedule until the delay is 2.33 times the length of the normal delay. In the case of a 5, participants will be instructed to revert to the day 12 delay (1.33 times the normal delay) for the remainder of the practice days. Participants will continue to fill out the paper-and-pencil daily monitoring log with the addition of questions about how difficult it was to delay the time to the first cigarette of the day on a scale of 1 = not at all difficult to 5 = extremely difficult and what strategies they used to delay the time to the first cigarette.

**Table 1 Tab1:** Examples of cognitive control regimens for the practice group

	Delay to 1st cigarette calculation	Example for smoker who smokes 1st cigarette of the day 5 min after waking and 2nd cigarette of the day 60 min later	Example for smoker who smokes 1st cigarette of the day 30 min after waking and 2nd cigarette of the day 90 min later
Baseline week (days 1–7)	Usual time	5 min	30 min
Day 8	Usual time + 0.33 of usual time to 2nd cigarette	~ 25 min	~ 60 min
Day 9	Usual time + 0.5 of usual time to 2nd cigarette	~ 35 min	~ 75 min
Day 10	Usual time + 0.66 of usual time to 2nd cigarette	~ 45 min	~ 90 min
Day 11	Usual time + 1.00 of usual time to 2nd cigarette	~ 65 min	~ 120 min
Day 12	Usual time + 1.33 of usual time to 2nd cigarette	~ 85 min	~ 150 min
Day 13	Usual time + 1.5 of usual time to 2nd cigarette	~ 95 min	~ 165 min
Days 14–20	Usual time + 1.66 of usual time to 2nd cigarette	~ 105 min	~ 180 min
Day 21 (follow-up fMRI)	Usual time	5 min	30 min

*fMRI* functional magnetic resonance imaging

##### No practice group

Participants in the no practice arm will not be instructed to change their smoking behavior in any way. Instead these participants will be instructed to smoke their cigarettes as usual over a 2-week period and to continue monitoring their smoking using the CO monitor and daily monitoring logs so that the study procedures for both arms are as similar as possible. The daily monitoring log will have an additional question asking whether they used CBT techniques at other times during the day to change or reduce their smoking. We chose a monitoring-only control arm to isolate the impact on brain activation of practicing skills following brief advice compared to any disruption in usual smoking behaviors engendered by monitoring itself [32].

#### Post-treatment scan appointment (day 21)

The post-treatment scan appointment will include the same self-report, behavioral, and fMRI procedures as the pre-treatment scan appointment (see Fig. 2). In addition, participants will complete an end-of-study assessment and debriefing including open-ended questions about the difficulty of the intervention, study experiences, and behavioral techniques employed to delay smoking the first cigarette of the day. Participants will also be given an overview of the goals of the study and anticipated outcomes to encourage engagement in research studies in the future. To promote retention and completion of daily questionnaires, participants will be compensated at the second visit for their time, for completing the 2 weeks of CO measurements (i.e., double the potential payment for the first week of measurements), and for returning the CO monitor.

### Measures

#### fMRI assessments

##### Image acquisition

Scanning will be performed on a 3-tesla Siemens Skyra scanner (Siemens, Erlangen, Germany) fitted with a 20-channel head and neck coil. Following automated scout image acquisition and shimming procedures to optimize field homogeneity, resting state, fMRI task, and structural scans will be acquired. Resting state scanning parameters will include BOLD sequences of 52 contiguous slices at a 40° angle to the anterior commissure–posterior commissure (AC-PC) line (repetition time/echo time [time repetition (TR)/time echo (TE)] = 3000/25 ms, flip angle = 90°, field of view = 640 × 640, matrix = 80 × 80, slice thickness = 3 mm, in plane resolution = 2.9 mm, 200 data points). Task scanning parameters will include gradient echo BOLD scans (five, one for each run of the craving rating task), which will be acquired in 43 contiguous oblique axial slices at a 40° angle (TR/TE = 2500/25 ms, flip angle = 90°, field of view = 560 × 560 mm, matrix = 80 × 80, slice thickness = 3.0 mm, in-plane resolution = 2.9 × 2.9 mm, 145 data points). Finally, a T1-weighted structural scan will be completed (3D MPRAGE sequence, TR/TE = 2300/2.95 ms, flip angle = 9°, field of view = 253 × 270 mm, matrix = 240 × 256, slice thickness = 1.2 mm, 176 slices). This scan will be used for Talairach transformation and coregistration with fMRI data. All participants will be positioned in the scanner so that the angle of the AC-PC plane is between 17° and 22° to the scanner coordinate space, ensuring that the 40° slice acquisition angle is constant for all participants. Preprocessing of resting and task fMRI data will be performed for each participant in AFNI (Medical College of Wisconsin).

##### Regulation-of-craving cognitive control task

During the ~ 30-min fMRI scan, participants will complete a regulation-of-craving task closely modeled after Kober et al. [23] in which they will view smoking and food cues and will be asked to rate “How much do you want this?” the items on a scale of 1 to 5 (1 = not at all; 5 = a lot) after viewing them (see Fig. 3). Smoking cues will include pictures such as people smoking and packs of cigarettes. Food cues will include pictures of appetizing food items such as pizza. All cues have been acquired from previous smoking and food cue reactivity studies [20, 23, 33, 34] and stock photography websites. Participants will receive instructions to regulate their responses to these images at the start of each trial. Half of the trials will be positive trials and half will be negative trials. In positive trials, participants will be instructed to think about the positive consequences of consuming the presented item. In negative trials, participants will be instructed to think about the negative consequences of consuming the presented item. A practice session will be conducted outside the scanner immediately prior to the scan to ensure that the participants understand the task. Following the imaging session, participants will be asked to describe the strategies they used during the task. Scanning will be done in five runs of 20 trials each (100 total trials), with trials of each of the four possible types—positive smoking, positive food, negative smoking, and negative food—presented in pseudorandom order. Participants will see different stimuli sets at each MRI appointment, which will be counterbalanced across participants. Stimuli will be presented using E-Prime 3 (Psychology Software Tools). Optimal timing of stimuli will be estimated using the Analysis of Functional Neuroimages (AFNI) stimulus timing program (make_random_timing.py).

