#### Analysis plan

The planned data analyses are built around three specific aims. The first aim is to compare changes in brain activation in cognitive control regions as a result of cognitive control practice. The second aim is to determine the effect of adherence to the practice regimen on changes in brain activation in cognitive control regions. The third aim is to explore the effects of individual differences (e.g., level of tobacco dependence, motivation, and sex) on changes in brain activation in cognitive control regions.

##### Aim 1

Our primary aim is to identify the impact of practicing delaying the first cigarette of the day compared to not practicing on functional brain activation changes in cognitive control regions. The percentage signal change when comparing the negative smoke condition to the positive smoke condition will be computed for our a priori cognitive control region of interest (ROI) (i.e., dlPFC) for each subject at each time point and entered into a two-way mixed-effects ANOVA model using the group (practice, no practice) × time (pre, post) interaction. We hypothesize that practice vs. no practice will lead to greater pre-to-post brain activation *increases* in the cognitive control network.

##### Aim 2

We will also identify the impact of *adherence* to practicing delaying cigarettes on functional brain activation changes in the cognitive control networks in response to smoking cues. Using only participants from the practice group, we will calculate Pearson correlations between differences in brain activation from the negative smoke and positive smoke conditions and amount of practice completed. Brain activation will be computed as percentage signal change from pre- to post-treatment in response to smoking cues in the a priori dlPFC ROI. Practice will be quantified as the proportion of time delayed from their usual first cigarette of the day to their second cigarette of the day and subjectively measured by participants’ perceived difficulty in delaying the first cigarette of the day. We hypothesize that greater levels of practice will show greater brain activation increases in the cognitive control network in response to negative smoke compared to positive smoke conditions from pre- to post-intervention.

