#### Power and sample size

The sample size was based on aim 1 and calculated based on changes in brain activation observed in pilot data following 1 week of practicing CBT skills and 2 weeks of CBT sessions. Assuming the no practice group will have a mean of 0 change in brain activation between day 7 and day 21, and equal variance in the two groups, our preliminary data suggest Cohen’s *d* effect sizes of 2.77 and 3.70 for dlPFC and vmPFC, respectively. These effect sizes suggest *n* = 5 and 4 subjects per group are required to achieve 80% power at 0.05/2 = 0.025 significance level (Bonferroni correction needed to compensate for tests involving each of two brain regions) in a two-sided two-sample *t*-test. However, the small sample in our pilot data (*N* = 6) also indicates wide 95% confidence intervals. Using the conservative estimates of the lower bound of the mean and upper bound of the standard deviation, the effect sizes are (0.0991/0.1415) = 0.70 and (0.2037/0.1889) = 1.08. Using a sample size of *n* = 40 per group provides 79% and > 99% power for dlPFC and vmPFC, respectively; the power will be greater if the actual effect sizes are larger than the conservative estimates.

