##### Regulation-of-craving task data preprocessing

The fMRI images will be realigned to the third slice collected in each scanning session to correct for motion. The images will be spatially smoothed with a 4-mm full width at half maximum (FWHM) Gaussian blur. Timepoints during which participants move more than 0.3 mm within a TR will be censored. Functional and anatomic images obtained within each session will be aligned and normalized to Talairach and Tournoux’s [35] stereotaxic atlas. Regressors representing the experimental conditions of interest (i.e., positive smoke, negative smoke, positive food, and negative food) will be modeled with a block response function and entered into the multiple-regression analysis using a random-effects model. Motion parameters will be included as nuisance regressors.

The primary contrast of interest will be negative smoke minus positive smoke, which represents an analog of the exertion of cognitive control minus general brain activation engendered by attending to smoking cues. The primary outcome analysis will focus on the a priori ROI, the dlPFC. In addition, an exploratory whole-brain analysis will be used to identify regions outside the dlPFC cognitive control network that may change with practice (e.g., the insula). The dlPFC ROI has been selected based on previous studies [5, 23, 24, 36]. The dlPFC will be defined using anatomical masks for the dlPFC based on the superior frontal gyrus and the middle frontal gyrus regions identified by AFNI’s whereami function. Multiple comparisons will be corrected using a familywise approach in which clusters will be considered significant at *p*_voxelwise_ < .01 and *p*_corrected_ < .05 within the dlPFC for the ROI analysis and within the whole-brain for the exploratory whole-brain analysis. The minimum cluster size will be determined using AFNI’s 3dClustSim function. The spatial autocorrelation function (acf) option was used in AFNI’s 3dFWHMx to estimate intrinsic smoothness and 3dClustSim to estimate the probability of false positives [37, 38]. The mean percentage signal change from dlPFC clusters that pass cluster thresholding will be used as the primary outcome data to test the hypothesis described in aim 1.

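### The named Aim 1 model has no term for stimulus set, although sets are swapped between scans; a set-by-instruction difference would cost some precision, and one extra term recovers it

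*Protocol article*

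**What the plan says.** The section on the regulation-of-craving task states: "Participants will see different stimuli sets at each MRI appointment, which will be counterbalanced across participants". It gives neither the number of sets nor the method of counterbalancing.

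The outcome is a within-session difference. The preprocessing section says: "The primary contrast of interest will be negative smoke minus positive smoke". Under Aim 1 of the analysis plan, the dlPFC value of this contrast at each scan is "entered into a two-way mixed-effects ANOVA model using the group (practice, no practice) × time (pre, post) interaction". No set or order term is named there or elsewhere in the article.

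On allocation, the article says: "Following the brief counseling, participants will be randomized using a 1:1 allocation ratio to the practice or no practice arm of the study". Counseling comes after the day 7 scan, so each participant has already seen the first set when the arm is assigned. The stratification factors do not include set order: "Groups will be stratified on gender and marijuana use to prevent these variables from confounding treatment effects".

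**The concern.** Counterbalancing separates stimulus set from scan across the sample, but not within a person. With two sets, one participant's change is measured from A to B and another's from B to A. If the sets differ in the analysed contrast by D, the first participant's change is shifted by +D and the second's by −D. The shift has a known sign for every participant, because the order is assigned by design. A model with only group and time treats it as random error.

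The primary test is the between-arm difference in change, and the article gives 79% power for the dlPFC. There is thus little reserve for avoidable residual variance in that test.

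**Working it through.** **Inputs** (protocol article, Power and sample size): "the effect sizes are (0.0991/0.1415) = 0.70 and (0.2037/0.1889) = 1.08", the first figure being for the dlPFC; 40 per arm; two-sided two-sample t-test; alpha 0.05/2 = 0.025; stated dlPFC power 79%.

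**Assumptions, not in the document:** two sets, A and B; half the participants in each order; D, the A-versus-B difference in the negative-minus-positive smoke contrast, expressed in units of the SD of change (0.1415).

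**Step 1: the plan's own figure.** With df = 2 × 40 − 2 = 78 and noncentrality 0.70 × √(40/2) = 3.13, the noncentral t gives power of 79.9% (80.0% with the unrounded ratio 0.0991/0.1415). The stated 79% is reproduced to within a point.

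**Step 2: which set differences matter.** Write the response to set s under each instruction as (overall level of s) + (instruction effect in s). In negative minus positive, the overall level drops out. Only a difference between sets in the instruction effect remains, and that is D.

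**Step 3: effect on the residual.** The change score carries +D or −D with equal frequency, which adds D² to its variance. So

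SD of change without a set term = 0.1415 × √(1 + D²), and effective d = 0.70 / √(1 + D²).

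| D (SD of change) | D (% signal change) | SD multiplied by | Effective d | Power | n per arm for 80% |
|---|---|---|---|---|---|
| 0 | 0 | 1.000 | 0.700 | 80.0% | 41 |
| 0.1 | 0.014 | 1.005 | 0.697 | 79.5% | 41 |
| 0.2 | 0.028 | 1.020 | 0.687 | 78.2% | 42 |
| 0.3 | 0.042 | 1.044 | 0.671 | 76.1% | 44 |
| 0.5 | 0.071 | 1.118 | 0.626 | 69.7% | 50 |

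**Step 4: check by simulation** (10,000 runs per scenario; D = 0, 0.3, 0.5 and 1.0; order either balanced by chance across arms or exactly balanced within arm).

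- The mean group × time estimate stays at the true value with or without the set term, so there is no bias.
- Without the term and with order falling by chance, type I error is about 0.025. With order balanced within arm it drops below nominal (roughly 0.02 at D = 0.3 and 0.001 at D = 1.0), because the estimated standard error is then too large.
- With a set-order term, power stays at 79–81% for every D simulated.

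**The case against.** The strongest reply is that counterbalancing is itself the remedy for set effects, and that nothing in the document suggests the sets differ in this contrast. Much of that stands. Counterbalancing keeps set from being confounded with time across the sample, and subtraction within a session removes any uniform difference in provocativeness. For D up to 0.2 SD the loss is under 2 points of power. The larger values are demanding: D = 0.5 SD is 0.071, or 0.071/0.0991 ≈ 71% of the mean change used for planning. On the other side, the article does not say that the same pictures serve both instructions within a set. If they do not, differences between pictures can enter the contrast directly.

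The planning SD is an upper confidence bound from a pilot of six, so it may leave room for extra variance. The document does not say whether the pilot used different sets. If it did, part of D² may already be in the 0.1415, and the set term would then raise power above the stated figure instead of protecting it.

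It can also be said that a one-degree-of-freedom nuisance term belongs in the analysis plan. That is fair as far as detail goes and is a reason to rate the point low. But the article does not leave the model open: it names a two-way model and lists its factors.

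A reader might go further and infer that set order is unbalanced between the arms and biases the comparison. The document does not support this. It does not state balance within arm, but it does not describe the counterbalancing method either, so imbalance is possible, not shown. As an illustration, suppose order were fixed at 40/40 overall and fell by chance between arms. The between-arm difference in the share with A first would have SD 0.11, with a 12% chance of reaching 20 percentage points. A 20-point difference would shift that trial's estimate by 2 × 0.20 × D = 0.4D, or 0.12 SD at D = 0.3. That chance shift is already part of the residual variance and the standard error, so it is the same precision loss seen in a single trial and not a second harm.

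**Conclusion.** The point holds as a matter of efficiency. The design assigns a stimulus order to each participant, and the named Aim 1 model does not use it. A difference between sets in the negative-minus-positive smoke contrast therefore stays in the residual of the pre-to-post change. Power falls from about 80% to 78%, 76% or 70% for D of 0.2, 0.3 or 0.5 SD of change. These figures rest on an assumed D, on two sets in equal numbers, and on the protocol's planning values.

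Three stronger readings should not be drawn: that any difference between sets matters, that the group × time estimate is biased in expectation, or that type I error is inflated. The stated power of 79% is not wrong on its own inputs. The point is minor, and worth acting on because the remedy is nearly free.

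**What to change.** Add stimulus set as a within-subject factor to the Aim 1 mixed model. With two sets this is equivalent to adding set order (A then B, or B then A) as a covariate in an analysis of change. State the term before the group data are analysed, so that its inclusion does not depend on the result. Tabulate set order by arm, which also settles whether order was balanced within arm.

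The cost is one degree of freedom (residual df 77 instead of 78 in the change analysis). No new data are needed, since the set shown at each scan is assigned by the design. If D is zero, essentially nothing is lost: simulated power with the term was still 79–80%.
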